##### Evolution of respiratory and hemodynamic parameters during NIV sessions

This analysis will be conducted according to the same principles as for the analysis of the evolution of respiratory comfort.

##### Adequacy of prescribed and observed NIV sessions duration

For this analysis, we will first calculate for each patient the ratio of the sum of the observed durations of NIV sessions and the sum of the prescribed durations. This ratio will reflect the compliance of each patient with the prescription. Compliance will be compared between groups by the usual tests for comparing a continuous outcome.

##### Number of interrupted sessions before the end of the prescribed duration

The number of interrupted sessions is a count outcome variable. The comparison groups will therefore be based on a Poisson regression model, introducing the randomization group as an explanatory variable and an "offset" variable (whose coefficient is not estimated and is fixed to 1) representing the number of prescribed sessions for each patient.

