### Total planned sample size

To take into account a potential loss to follow-up of about a 5 % rate for the primary endpoint, we expect to randomize a total of 99 participants (33 per arm).

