#### Other analyses

All secondary analyses will be performed in the intention-to-treat population (all randomized patients) and also in the per protocol population (patients with no major deviation of the protocol) at a bilateral 5 % alpha risk.

Unless otherwise specified, categorical variables will be compared by a chi-squared test or Fisher test as appropriate. Continuous variables will be compared by a Student's *t* test or Wilcoxon test as appropriate (when two groups are compared) and by an analysis of variance (ANOVA) or Kruskal-Wallis test as appropriate (when more than two groups are compared).

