##### Evolution of respiratory comfort during NIV sessions

The number of measures of respiratory comfort for each patient will be variable, since the duration and number of NIV sessions is at the discretion of the physician. The data structure is complex and has three levels:Level 1: respiratory discomfort measuresLevel 2: patientsLevel 3: centers.

For this type of (repeated) data, it is essential to take into account correlations between measurements from the same patient. A linear mixed effects model (including fixed and random effects) will be used to model the effect of the three interventions on the evolution of respiratory comfort during NIV sessions. This model will include:Fixed effects○ The variable "time"○ The randomization group (categorical variable with three different levels) and its interaction with time○ Stable characteristics over time (see potential confounders described above)○ Characteristics which vary over time: the number of NIV sessionsRandom effects ("subject effect").

The need for a model with random intercept and slope (versus random intercept only) will be assessed at the time of the analysis with a likelihood ratio test. An appropriate modeling of time will be performed if its effect is not linear.

Correlations between patients from the same center could also be taken into account by the inclusion of a "random center effect" (level 3). However, such a mixed model may be unsuitable in practice because of the limited number of clusters (only three participating centers). In this setting, it is preferable to include a fixed center effect [33], and this is the solution that will be implemented in this analysis.

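### Interrupted sessions: a plain Poisson model is fixed with no allowance for patients who differ in their tendency to interrupt, so the stated 5 % test level is not assured

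*Protocol article*

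**What the plan says.** In the Protocol article, the section *Number of interrupted sessions before the end of the prescribed duration* begins: "The number of interrupted sessions is a count outcome variable". From this it concludes: "The comparison groups will therefore be based on a Poisson regression model". Randomization group is the only explanatory variable named. The offset is described as one "whose coefficient is not estimated and is fixed to 1) representing the number of prescribed sessions for each patient". The section names no dispersion parameter, robust variance or patient effect, and no alternative if the Poisson variance does not fit.

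The endpoint is one of eleven under *Secondary endpoints*. *Other analyses* tests these "at a bilateral 5 % alpha risk". On arm size: "we expect to randomize a total of 99 participants (33 per arm". On exposure, *Evolution of respiratory comfort during NIV sessions* says that "the duration and number of NIV sessions is at the discretion of the physician". For repeated comfort scores the same section states that "it is essential to take into account correlations between measurements from the same patient", and it plans a mixed model with a subject effect.

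**The concern.** Each prescribed session either is or is not cut short, and one patient contributes several sessions. The count is therefore a number of events out of a known number of trials, and it cannot exceed that number. This makes its variance smaller than Poisson when all patients share the same interruption probability, and larger when some patients interrupt often and others never. Plain Poisson standard errors are right only where the two effects happen to cancel.

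The article accepts the principle for comfort scores and does not carry it over to interruptions in the same patients. Its *Definitions* section equates NIV intolerance with premature cessation of a session, and tolerance is the trial's hypothesis. A nominally significant result here would be read as support for the intervention. At stake is whether the 5 % level attached to that result means 5 %.

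**Working it through.** The article gives no figure for this analysis, so there is none to reproduce.

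**Inputs.** From the article: 3 arms of 33, two-sided 5 %, Poisson model with group as the only covariate. Assumed: mean sessions m = 6, interruption probability p = 0.2, within-patient correlation ρ from 0 to 0.2, no arm effect, beta-binomial counts, and a 2-df likelihood-ratio test of the three arms with log(sessions) as offset.

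**Variance ratio.** With equal session numbers, variance/mean = (1 − p)(1 + (m − 1)ρ). The Poisson model assumes 1.
- ρ = 0: 0.8 × 1 = 0.8
- ρ = 0.1: 0.8 × 1.5 = 1.2
- ρ = 0.2: 0.8 × 2 = 1.6
- Break-even: ρ = p / [(1 − p)(m − 1)] = 0.2 / (0.8 × 5) = 0.05

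With unequal session numbers S, the ratio for an arm total replaces m by E[S²]/E[S].
- 1 + Poisson(5): variance 5, so (36 + 5)/6 = 6.83. The ratio is 0.8(1 + 5.83ρ), which is 1.27 at ρ = 0.1 and 1.73 at ρ = 0.2.
- Geometric with mean 6: variance 30, so (36 + 30)/6 = 11. The ratio is 0.8(1 + 10ρ), which is 1.6 at ρ = 0.1 and 2.4 at ρ = 0.2.

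**Type I error.** If the true variance is φ times Poisson, the 2-df test rejects with probability of about exp(−5.991/(2φ)) = 0.05^(1/φ). The simulated column comes from 10,000 null trials per setting.

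| ρ | Sessions per patient | φ | 0.05^(1/φ) | Simulated |
|---|---|---|---|---|
| 0 | all equal, or geometric | 0.8 | 2.4 % | 2.3 % |
| 0.1 | all equal | 1.2 | 8.2 % | 8.4 % |
| 0.1 | 1 + Poisson(5) | 1.27 | 9.4 % | – |
| 0.1 | geometric | 1.6 | 15.4 % | 14.5 % |
| 0.2 | all equal | 1.6 | 15.4 % | 15.7 % |
| 0.2 | 1 + Poisson(5) | 1.73 | 17.8 % | – |
| 0.2 | geometric | 2.4 | 28.7 % | 28.6 % |

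A separate simulation gave about 2 %, 9–14 % and 17–27 % at ρ = 0, 0.1 and 0.2, in line with the table.

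A single two-arm contrast is less affected. With 1 + Poisson(5) sessions and 1,500 trials per setting, it rejected in 3.5, 7.5, 12.2 and 16.3 % at ρ = 0.01, 0.09, 0.17 and 0.25.

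Over a wider grid (mean sessions 3 to 10, p from 0.1 to 0.4, ρ from 0 to 0.3) the three-arm test ran from about 0.6 % to 57 %.

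**Candidate remedies.** Pearson (quasi-Poisson) scaling averages over patients, so it estimates 0.8(1 + 5ρ) even when session numbers vary. For geometric counts at ρ = 0.2 it supplies 1.6 where 2.4 is needed. The remaining ratio is 2.4/1.6 = 1.5, and 0.05^(1/1.5) = 13.6 %; the simulations gave 12–13 %. A robust variance uses the squared residuals of each patient directly and gave about 5.5–8 % for ρ from 0 to 0.2.

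**The case against.** **The offset.** A reader might infer that the untransformed number of sessions enters as the offset, which would make expected counts grow exponentially with sessions. The text does not support this. A coefficient fixed at 1 is what defines an offset, and saying that the variable represents the number of sessions is ordinary shorthand for log exposure under a log link. In one simulated data set the raw number gave a deviance of 1900 on 96 df, against 82 with the log, so it is not a plausible plan. At most, the words log of could be added for clarity.

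**The direction.** A reader might also infer that the p-values are wrong, or that false positives must exceed 5 %. That is not established. The article gives no interruption rate, session distribution or within-patient correlation. Below the break-even correlation the test is conservative, and how strongly interruptions cluster is not known from the document.

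**Level of detail.** Dispersion checks are often left to an analysis plan, which is not shown, and no sample size or confirmatory claim depends on this endpoint. The related ratio of observed to prescribed duration takes one value per patient and does not use the Poisson variance. These points hold and keep the priority low. They do not remove the concern. The article names fallbacks elsewhere (a Wilcoxon test if t-test conditions fail, a likelihood-ratio test for random slopes) but commits to a single model here, against its own principle for repeated measurements.

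**Conclusion.** The concern stands in conditional form. A plain Poisson variance does not suit repeated yes/no results in the same patients, and the article makes no provision for this. At 6 sessions on average and 20 % interrupted, the three-arm test falls short of its nominal level when ρ is below about 0.05 and exceeds it above that. The error is about 2 % at ρ = 0, 9–14 % at 0.1 and 17–27 % at 0.2, the higher values applying when session numbers vary widely. Only the arm size comes from the article; the rest is assumed, so these figures show sensitivity and do not predict the trial's error rate. This is a cheap improvement to a secondary analysis. It does not touch the primary endpoint or the sample size.

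**What to change.** Replace the model sentence with: *Poisson regression with log link, randomization group as explanatory variable, offset log(number of prescribed sessions) and robust (sandwich) variance; effects reported as rate ratios with 95 % CI.* A beta-binomial model, or a session-level logistic model with a patient random effect, would also serve, with the effect and its 95 % CI reported on that model's own scale.

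Quasi-Poisson scaling alone is only a partial remedy when session numbers vary widely. A negative binomial model cannot represent the underdispersed case.

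The cost is one sentence and no new data. Relative to plain Poisson, standard errors change by √φ: narrower by a factor √0.8 = 0.89 if patients are alike, and wider by √1.2 = 1.10 to √2.4 = 1.55 for ρ between 0.1 and 0.2 under the assumptions above. Wider intervals are the price when patients differ. A slight excess over 5 % remains at this sample size (about 5.5–8 % with the robust variance).

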##### Percentage of patients requiring physical restraints or administration of anxiolytics or sedatives during NIV sessions, percentage of intubated patients

These percentages will be compared between groups by the usual tests for comparing proportions.

##### SF-36, HADS scores, IES-R scores, and overall assessment of NIV between inclusion and day 90

The evolution of these scores between baseline and day 90 (difference between the measurement at 3 months and inclusion) will be compared between groups by the usual tests comparing continuous variables.

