## Data collection and follow-up

Collected data at each time are summarized in the SPIRIT schedule of events shown in Table 1.

**Table 1 Tab1:** Summary of collected data at each time point according to SPIRIT 2013 guidelines

			Study period							
	Enrollment	Allocation	Post-allocation — at each NIV session						NIV discontinuation, ICU discharge or day 28	Close-out Day 90
Time point			*t* _1_ beginning of NIV session	*t* _2_(*t* _1_ + 5 min)	*t* _3_(*t* _1_ + 30 min)	*t* _4_(*t* _1_ + 1 h)	*t* _*x*_ ^a^	End of each NIV session		
Enrollment:										
Eligibility screen	X									
Informed consent	X									
Allocation		X								
Interventions:										
Musical intervention										
Sensory deprivation										
Control group										
Assessments:										
*Baseline variables:* Demographic data and medical history, SAPS III, SOFA	X									
*Outcome variables:* Respiratory comfort, RASS			X	X	X	X	X	X		X
Respiratory and hemodynamic parameters		X	X	X	X	X	X	X		
*Ongoing therapies:* Catecholamine infusion, need for ETI, attempts to pull out NIV mask, headphones or sensory isolation, need for physical contention, sedative or anxiolytic treatments, NIV complication		X						X		
Health-related quality of life (HADS and SF-36 scores)		X								X
Length of ICU and hospital stay										X
Vital status, NIV satisfaction, comfort and associated trauma, IES-R for NIV									X	X
Decision to withhold life-sustaining therapies									X	

*NIV* non-invasive ventilation, *ETI* endotracheal intubation, *HADS* Hospital Anxiety and Depression Scale [28], *IES-R* Impact of Event Scale - Revised [31], *RASS* Richmond Agitation-Sedation Scale [30], *SAPS III* Simplified Acute Physiological Score III [26], *SF-36* Short Form-36 [29], *SOFA* Sequential Organ Failure Assessment [27]

^a^
*t*
_*x*_ stands for *t*
_1_ + 2, 3, 4, 6, 8, 12, 16, 20, 24 hours depending on the length of each NIV session

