### At day 1 (baseline)

Demographic data and medical history, including the current clinical history with the reason for ICU admission, Simplified Acute Physiology Score III severity score [26], and Sequential Organ Failure Assessment score [27], are collected.

Treatments including NIV (and its settings), fluid therapy, catecholamine infusion, and endotracheal intubation are recorded. Laboratory tests include serum (and urine if diuresis is present) electrolyte levels determination, serum glucose level, urea and creatinine concentration, and arterial blood gas determination. Respiratory and hemodynamic parameters before the beginning of the NIV session (respiratory rate, exhaled tidal volume, PaO_2_/FiO_2_ ratio, heart rate, arterial pressure) are collected.

The research team administers to the patient, or to a proxy if the patient is not able to answer, the baseline Hospital Anxiety and Depression Scale (HADS) questionnaire [28] and Short Form-36 (SF-36) [29] in order to determine the baseline health-related quality of life.

### At each NIV session, until NIV discontinuation or day 28

The prescribed duration of the NIV session is recorded. Prior to each NIV session, immediately after NIV is correctly set (5 minutes), at 30 minutes, and at 1, 2, 3, 4, 6, 8, 12, 16, 20, 24 hours depending on the length of each NIV session, and at the end of the session, the following data are collected:Respiratory comfort assessed by a blinded evaluator (nurse from another unit) with the use of a numeric visual scale [14]The same respiratory and hemodynamic parameters as the initial onesAgitation assessed by Richmond Agitation-Sedation Scale [30].

For each NIV session, the need for physical contention or sedative or anxiolytic treatments is assessed and recorded. The tolerance of sensory isolation is recorded, as well as attempts to pull off the NIV mask or headphones. At the end of each session, data for its exact duration, the reason of its premature ending if appropriate, and the need for endotracheal intubation are collected. Furthermore, arterial blood gases are reported when these tests are performed as clinically indicated. The occurrence of nasal bridge ulcers or irritations is also recorded. For the “musical intervention” group, the type of music chosen and the feeling experienced during the session are recorded.

### At NIV discontinuation, ICU discharge, or day 28

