Apart from endotracheal intubation, the need for tracheostomy during the ICU stay and vital status at ICU discharge are recorded. Patients are surveyed for numeric scaling of NIV satisfaction, NIV comfort, and NIV-associated trauma. The Impact of Event Scale - Revised (IES-R) [31] is applied to NIV.

### At day 90

Vital status is regularly updated for each patient until the end of the study. In order to determine the 3-months health-related quality of life, numeric scaling of NIV satisfaction, NIV comfort, and NIV-associated trauma, the IES-R applied to NIV, and the HADS questionnaire [28] and SF-36 [29] are determined and recorded by a blinded-to-randomization group research staff member through a phone survey of patients who are alive.

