### Statistical analysis

A flow chart will describe the number of eligible patients and the number of patients actually included (in total and per arm). For each group and at each assessment date, qualitative variables will be described in terms of number and percentage, and quantitative variables in terms of number, mean, and standard deviation. Quantitative variables with skewed distribution will be presented in terms of median and interquartile range (25th–75th percentile).

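### IES-R and overall NIV assessment are to be analysed as change from inclusion, but neither is scheduled at inclusion, so the stated change score cannot be computed for these two secondary endpoints

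*Protocol article*

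**What the plan says.** **Analysis.** Near the end of the Statistical analysis section, one heading covers four outcomes: "SF-36, HADS scores, IES-R scores, and overall assessment of NIV between inclusion and day 90". A single rule follows for all of them: "The evolution of these scores between baseline and day 90 (difference between the measurement at 3 months and inclusion) will be compared between groups", using the usual tests for continuous variables. The words in parentheses identify baseline with inclusion.

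**Data collection.** At day 1 the research team administers the "baseline Hospital Anxiety and Depression Scale (HADS) questionnaire [28] and Short Form-36 (SF-36) [29] in order to determine the baseline health-related quality of life". No other questionnaire is named there. The section for NIV discontinuation, ICU discharge or day 28 is the first place where the NIV-specific instruments appear: "Patients are surveyed for numeric scaling of NIV satisfaction, NIV comfort, and NIV-associated trauma", and "The Impact of Event Scale - Revised (IES-R) [31] is applied to NIV". Both are repeated by telephone at day 90.

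**Schedule of events (Table 1).** The row "Vital status, NIV satisfaction, comfort and associated trauma, IES-R for NIV" is marked in the column for NIV discontinuation, ICU discharge or day 28 and in the day-90 column, and nowhere else. The HADS and SF-36 row is marked at allocation and at day 90.

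**Secondary endpoints.** HADS and SF-36 are listed at baseline and 3 months. IES-R and overall assessment of NIV are listed at discontinuation and at 3 months or day 90.

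**The concern.** The plan keeps two pairs of instruments apart everywhere except in the analysis rule. HADS and SF-36 describe the patient's general state and have a baseline. IES-R applied to NIV and the NIV ratings describe the experience of NIV and are first taken when NIV ends. The rule applies the first pair's change score to the second pair, where its starting value is not scheduled.

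What is at stake is a clear prespecified contrast for two endpoints that the Discussion presents as part of the trial's patient-centred purpose. The Discussion also wants NIV-related stress assessed both early and late, to judge how long any effect lasts. That calls for a comparison between arms at each time, and the rule supplies neither. An analyst who finds that the rule cannot be run has to choose a replacement. In an open-label trial that choice is better made before the comparisons by arm are seen.

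**Working it through.** The plan gives no figure to reproduce here. The check is whether both terms of the stated difference are scheduled for each outcome.

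| Outcome | Inclusion | NIV discontinuation, ICU discharge or day 28 | Day 90 | Day 90 minus inclusion |
|---|---|---|---|---|
| HADS | yes | no | yes | computable |
| SF-36 | yes | no | yes | computable |
| IES-R applied to NIV | no | yes | yes | not computable |
| Overall assessment of NIV | no | yes | yes | not computable |

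Sources: the day-1, discontinuation and day-90 parts of Data collection and follow-up; Table 1; Secondary endpoints. Table 1 was read from a PDF, but the running text and the endpoint list give the same time points independently, so the result does not depend on the table's layout.

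**Can the missing term be recovered?** The Missing data section plans multiple imputation from observed data. With no inclusion value of IES-R or the NIV ratings scheduled for any patient, there is nothing observed at that time from which to impute.

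**What if the discontinuation score stood in for the inclusion score?** The plan does not propose this, but it is the nearest substitute. Let d_D and d_90 be the true differences between two arms at discontinuation and at day 90. The difference between arms in the change score is then

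d_90 − d_D.

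Write d_D = f × d_90. The contrast becomes (1 − f) × d_90. The documents give no value for f, so the following values are assumptions chosen to show the range:

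- f = 0 (no difference at discontinuation): 1 × d_90, nothing lost.
- f = 0.5: 0.5 × d_90, half lost.
- f = 1 (equal difference at both times): 0, all lost.
- f = 2 (the difference halves by day 90): −1 × d_90, the sign is reversed.

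The discontinuation score is measured after randomisation and can carry the treatment effect, so subtracting it removes whatever difference is already there.

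**The case against.** Several points can fairly be made on the plan's side.

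**The discontinuation score is not ignored.** A reader might infer that it goes unused, or that the two endpoints would have no result at all. The documents do not support that. The general descriptive rule ("For each group and at each assessment date, qualitative variables will be described in terms of number and percentage, and quantitative variables in terms of", after which come the usual summary measures) covers the discontinuation assessment. Under Other analyses there are default tests for continuous variables, which might be read to extend to that score, and the endpoint list names the time point. What stands is narrower. Those defaults apply where nothing else is laid down, and for these outcomes something else is laid down that cannot be run. No specific between-group analysis is stated for the discontinuation score.

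**An inclusion value is not impossible in principle.** A reader might infer that no rating of NIV can exist before the trial's first session. The Study population section says that patients treated with NIV are screened, and the primary endpoint refers to the first session after randomisation, so some patients may have had NIV earlier. The supported statement is that no inclusion measurement is scheduled.

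**The cancellation argument is not about the plan's own analysis.** Nothing in the documents uses the discontinuation score as a baseline, and complete cancellation requires equal arm differences at both times. Change from discontinuation to day 90 is also a legitimate quantity, namely how the difference evolves. It does not answer whether the arms differ at either time. The argument therefore stands as a caution about the repair, not as a bias in the plan.

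**It may be no more than a merged heading.** That is plausible, since the endpoint list already gives the right time points. But the analysis text as written is wrong for two outcomes; it is not merely brief, and an unseen analysis plan would have to contradict it in order to correct it.

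**Conclusion.** The point holds as an internal contradiction of moderate importance. For two of the four outcomes under the rule, IES-R applied to NIV and overall assessment of NIV, the inclusion value is absent for every patient by design, so the stated change score cannot be computed. No specific between-group analysis is stated for the discontinuation score.

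This rests only on the time points given in the article, which agree across three places. It needs no assumption about effect sizes.

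A reader might go further and infer that the HADS and SF-36 analysis is also faulty, or that the trial's main conclusion is at risk. Neither follows. HADS and SF-36 are scheduled at both times, and their change score is computable and is a valid randomised comparison. The affected outcomes are secondary; the primary endpoint, its hierarchical test procedure and the sample size do not involve them.

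**What to change.** Split the rule into two.

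1. **IES-R and overall assessment of NIV:** compare the scores themselves between arms at NIV discontinuation (or ICU discharge or day 28, as in the data collection section) and, separately, at day 90, with the tests already named for continuous variables. This matches the endpoint list. State that the discontinuation score is an outcome and will not serve as a baseline. If change from discontinuation to day 90 is of interest, label it as a description of how the difference evolves, in addition to the two comparisons.
2. **HADS and SF-36:** keep the inclusion-to-day-90 analysis. Comparing day-90 scores adjusted for the collected baseline score is an optional gain in precision, not the correction of an error.

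The cost is a change of analysis wording. No visit, questionnaire or patient is added, because the measurements are already scheduled. The article reports enrolment as ongoing; the change should be recorded before these outcomes are compared by arm.
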